**Table 3B | Linear regression (outcome: PHQ-9 total score).**			
**Predictor**	**Model**	**β (SE)**	***P*-value**
Dorsalis pedis RI (per 0.1 increase)	Model A (basic)		
Dorsalis pedis PI (per 0.1 increase)	Model A (basic)		
Monophasic vs. triphasic waveform	Model B (extended vascular)		
baPWV (per 100 cm/s increase)	Model B (extended vascular)		
ABI (per 0.1 increase)	Model B (extended vascular)		
SDNN (per 10 ms increase)	Model C (with HRV)		
RMSSD (per 10 ms increase)	Model C (with HRV)		
Age (per 10-year increase)	All models (adjusted)		
Female sex	All models (adjusted)		
BMI (per 1 kg/m^2^ increase)	All models (adjusted)		
Hypertension	All models (adjusted)		
Diabetes mellitus	All models (adjusted)		
Dyslipidaemia	All models (adjusted)		
OLGA stage III/IV vs. 0–II	All models (adjusted)		

#### Incremental value analysis

3.5.4

Three hierarchical models for identifying PHQ-9 ≥ 10 at baseline will be compared:

① Model A (Clinical-GI Model): Demographics + cardiovascular risk factors + gastritis severity

② Model B (Vascular Multimodal Model): Model A + dorsalis pedis ultrasound + baPWV/ABI/TBI

③ Model C (Extended Multimodal Model): Model B + HRV metrics (e.g., SDNN, RMSSD)

Area under the ROC curve (AUC) and 95% CI will compare model performance. Among model-performance measures, AUC will be treated as the primary discrimination metric, whereas calibration indices, Brier score, and decision-curve analysis will be considered supplementary or secondary performance assessments. Model calibration will be assessed using calibration plots and, where appropriate, calibration slope/intercept and Brier score. We will additionally consider decision-curve analysis to evaluate potential clinical utility across plausible referral thresholds.

The primary inferential analysis will be a prespecified multivariable logistic regression model for PHQ-9 ≥ 10 including a limited set of predefined vascular exposures and major confounders. Linear models for PHQ-9 total score, penalized regression, composite-score approaches, and decision-curve analysis will be considered secondary or exploratory analyses. In the primary model, vascular predictors will be limited to a small prespecified set of clinically interpretable measures, such as dorsalis pedis RI and/or PI together with baPWV, while additional vascular or autonomic variables will be evaluated only in secondary or exploratory analyses.

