### Multimodal data collection (study procedures)

3.3

All enrolled participants undergo a standardized multimodal evaluation protocol, comprising the following four primary domains. Adjusted covariates will include age, sex, body mass index, smoking, alcohol use, education level, marital status, hypertension, diabetes, dyslipidemia, Helicobacter pylori status, medication use, and OLGA/OLGIM stage.

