##### Blood pressure and heart rate

3.3.3.1

Resting seated or supine measurements are taken using an automated monitor, repeated 2–3 times with the average recorded for systolic/diastolic BP and resting HR.

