##### HRV

3.3.3.2

Short-term (5-min) HRV is recorded in a quiet, appropriately lit setting using a 3-lead ECG or RR interval–capable device. Recordings will be obtained during spontaneous breathing under standardized posture (supine or seated), with participants resting quietly throughout the procedure. Respiratory rate will be documented when feasible, and residual variation related to breathing pattern will be acknowledged as a potential limitation in interpretation. Accordingly, HRV-related findings will be interpreted cautiously in view of the potential residual confounding introduced by uncontrolled respiratory variation. Device sampling specifications will also be documented. R-wave detection and artifact removal are performed using validated software, and time-domain metrics are calculated, including:

① SDNN (standard deviation of normal-to-normal intervals).

② RMSSD (root mean square of successive differences).

③ Frequency-domain analyses may also be performed if applicable.

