#### Multivariable models

3.5.3

Logistic regression will assess the independent association between key vascular markers (e.g., dorsalis pedis RI, PI, waveform classification, baPWV, ABI/TBI) and PHQ-9 ≥ 10, adjusting for study center (as a fixed effect), age, sex, body mass index, smoking status, alcohol use, education level, marital status, hypertension, diabetes, dyslipidemia, relevant medication use, and histopathological severity (e.g., OLGA/OLGIM stage or Updated Sydney graded atrophy/intestinal metaplasia). Results will be reported as odds ratios (OR) with 95% confidence intervals (CI). We will restrict the number of predictors in the primary multivariable models to approximately 10–12, prioritizing predefined key vascular indices and major confounders, with additional variables explored only in sensitivity analyses.

In a secondary analysis, linear regression will evaluate the association between vascular indices and PHQ-9 as a continuous outcome. Prior to model fitting, collinearity among vascular indices (e.g., RI, PI, baPWV, ABI/TBI) will be assessed (e.g., via variance inflation factors); if substantial collinearity is detected, we will reduce the number of simultaneously entered vascular predictors or construct composite scores to improve model stability. Model assumptions will be checked; transformations or generalized linear models will be applied as needed. Continuous predictors will be modeled linearly in the primary analysis unless clear evidence of non-linearity is identified; if linearity assumptions appear violated, appropriate transformations or restricted spline terms will be explored in secondary analyses. The results of the prespecified logistic and linear regression analyses will be presented in Table 3.

**TABLE 3 T3:** Multivariable associations between vascular measures and depressive symptoms.

Table 3A | Logistic regression (outcome: PHQ-9 ≥ 10).			
Predictor	Model	OR (95% CI)	*P*-value
Dorsalis pedis RI (per 0.1 increase)	Model 1 (basic)		
Dorsalis pedis RI (per 0.1 increase)	Model 2 (extended)		
Dorsalis pedis PI (per 0.1 increase)	Model 1 (basic)		
Dorsalis pedis PI (per 0.1 increase)	Model 2 (extended)		
Monophasic vs. triphasic waveform	Model 2 (extended)		
baPWV (per 100 cm/s increase)	Model 2 (extended)		
ABI (per 0.1 increase)	Model 2 (extended)		
SDNN (per 10 ms increase)	Model 3 (with HRV)		
RMSSD (per 10 ms increase)	Model 3 (with HRV)		
Age (per 10-year increase)	All models (adjusted)		

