Female sex	All models (adjusted)		
BMI (per 1 kg/m^2^ increase)	All models (adjusted)		
Hypertension	All models (adjusted)		
Diabetes mellitus	All models (adjusted)		
Dyslipidaemia	All models (adjusted)	–	–
OLGA stage III/IV vs. 0–II	All models (adjusted)	–	–
Model 1: adjusted for age, sex, body mass index (BMI), and conventional cardiovascular risk factors. Model 2: Model 1 plus histological severity of gastritis and standard arterial stiffness/peripheral artery indices (baPWV and ABI/TBI). Model 3: Model 2 plus heart rate variability (HRV) indices.			

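### Resting heart rate is recorded but enters no model, so the secondary HRV step cannot separate heart rate variability from pulse rate

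*Protocol article*

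**What the plan says.** Section 3.5.4 builds three nested models. The base is "Model A (Clinical-GI Model): Demographics + cardiovascular risk factors + gastritis severity". Model B adds dorsalis pedis ultrasound and baPWV/ABI/TBI. The last tier is "Model C (Extended Multimodal Model): Model B + HRV metrics (e.g., SDNN, RMSSD"). The footnote to Table 3A does the same for the association models: "Model 3: Model 2 plus heart rate variability (HRV) indices". Table 3B repeats the step as its own Model C. Both tables report SDNN and RMSSD per 10 ms.

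Section 3.3.3.2 defines the indices on the raw beat-to-beat interval, for example "RMSSD (root mean square of successive differences"), with no correction for rate.

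Section 3.3.3.1 has an automated monitor take the vital signs, "repeated 2–3 times with the average recorded for systolic/diastolic BP and resting HR". The only planned use of that heart rate is one row of Table 2. It is absent from:

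- the general list in Section 3.3, whose one further item is histological staging: "Adjusted covariates will include age, sex, body mass index, smoking, alcohol use, education level, marital status, hypertension, diabetes, dyslipidemia, Helicobacter pylori status, medication use";
- the logistic adjustment list in Section 3.5.3, which ends "marital status, hypertension, diabetes, dyslipidemia, relevant medication use, and histopathological severity";
- every row and the footnote of Table 3A, every row of Table 3B, and the three tiers of Section 3.5.4.

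Model A's cardiovascular risk factors are a loose label. Where the article itemises its adjustment variables, it names smoking, hypertension, diabetes and dyslipidemia, and never heart rate.

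**The concern.** Objective 3 asks what HRV adds over clinical and histological variables. Pulse rate is about the cheapest clinical variable there is, since it comes with the blood pressure reading. SDNN and RMSSD each carry a heart-rate component. A comparison of Model B with Model C, or of Model 2 with Model 3, is thus a comparison of neither measure with a blend of both.

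If screen-positive patients simply have faster hearts, SDNN and RMSSD would show inverse odds ratios even if variability told nothing more. The reader could not see this from the planned tables, and a finding reached by a 5-minute recording might be one that a pulse reading already gives.

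**Working it through.** **The plan's own figures.** The article gives no figure for the HRV increment. Its sample size sets the scale: 10 events × 10–12 predictors = 100–120 events; 100/0.25 = 400 and 120/0.25 = 480; 400/0.9 ≈ 445 and 480/0.9 ≈ 534. The stated target of 450–520 is within 3% of these.

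**Why the indices depend on rate.** With RR = 60,000/HR in ms, SD(RR) ≈ (60,000/HR²) × SD(HR). Successive differences scale by the same factor. For an assumed fluctuation of 3 bpm at every mean rate:

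| Mean HR (bpm) | 60,000/HR² × 3 | SDNN (ms) |
|---|---|---|
| 60 | 16.67 × 3 | 50 |
| 70 | 12.24 × 3 | 37 |
| 80 | 9.38 × 3 | 28 |
| 90 | 7.41 × 3 | 22 |

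From 60 to 90 bpm SDNN falls by more than half (22/50 = 0.44) through mean rate alone. A constant 3 bpm is a simplification, so the table shows the direction and order of the effect and is not a forecast.

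**How often HRV would look informative.** Assumptions, none of them in the documents: 480 evaluable patients, 25% events, six other predictors, ln RMSSD correlated −0.4 or −0.6 with heart rate, ln SDNN correlated 0.8 with ln RMSSD, and no HRV effect given heart rate. There were 1,500 simulated studies per scenario, with a 2-df likelihood-ratio test of the HRV pair at 0.05:

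| OR per SD of heart rate | Correlation | Without heart rate | Heart rate in both models |
|---|---|---|---|
| 1.2 | −0.4 | 8.9% | 4.8% |
| 1.2 | −0.6 | 13.2% | 6.1% |
| 1.3 | −0.4 | 13.5% | 5.8% |
| 1.3 | −0.6 | 25.1% | 5.2% |
| 1.4 | −0.4 | 19.1% | 4.8% |
| 1.4 | −0.6 | 36.6% | 5.2% |

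The apparent odds ratio per SD of HRV is 0.82–0.93.

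A separate simulation (485 patients, eight other predictors, HRV in ms, correlations −0.3 to −0.7, 500 studies per scenario) agrees. At OR 1.3 it rejects in 11–32% without heart rate. At OR 1.0 it rejects in about 5%, so there is no false signal unless heart rate itself relates to the outcome. With heart rate in both models it rejects in 4–7% throughout.

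**What happens to AUC, the plan's primary discrimination metric.** In the scenarios of the table above (300 studies each, with assumed effects for the other predictors), the large-sample gain of C over B is 0.001–0.010. The mean out-of-sample gain, which optimism correction aims at, is −0.003 to +0.005. It is zero or negative in 10–65% of studies and above 0.02 in none. The separate simulation gives a large-sample gain of 0.002–0.012 at OR 1.3, and 0.000 once heart rate is in both models. A gain as large as 0.040 needs OR 1.8 with a correlation of −0.7.

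**The case against.** The strongest reply has four parts.

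- **The metric.** The plan does not test the HRV pair by likelihood ratio. It compares AUCs with bootstrap optimism correction, and on that scale the false gain is small. This stands. The joint test is a stand-in for the Table 3 HRV estimates; the rate for either single P-value was not worked out. Section 4.3 also says that significance alone will not drive interpretation.
- **The framing.** The protocol files resting heart rate under autonomic measures, both in Section 3.3.3 and in Table 2. Signal shared by heart rate and HRV can then be called autonomic information, and adjustment may remove some of it. This also stands. It is a reason to show both versions, but objective 3 names HRV specifically, so the shared part should not be credited to HRV unseen.
- **The stakes.** Section 3.5.4 keeps autonomic variables out of the primary model, and the study calls itself exploratory. This stands and limits the weight of the point.
- **Existing safeguards.** Medication including β-blockers is adjusted for, HRV is to be read cautiously because of breathing, and residual confounding by autonomic state is acknowledged. Table 2 would show a heart-rate difference between groups. None of these puts heart rate into a model. Optimism correction does not help either: it removes overfitting, whereas this would be a real association credited to the wrong measure.

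A reader might infer that Model C will visibly beat Model B and the study will end up endorsing an ECG recording. The AUC results do not support that, and the article requires external validation before any clinical use.

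**Conclusion.** The point holds for the secondary HRV step. As specified, neither B to C nor Model 2 to Model 3 (nor the Table 3B counterpart) can distinguish variability from pulse rate.

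Under the assumed OR of 1.2–1.4 per SD of heart rate and correlation of −0.4 to −0.6, HRV terms with no effect of their own would be jointly significant in roughly 9–37% of studies, while the corrected AUC gain would be about 0.01 or less. The exposure therefore lies mainly in the HRV estimates of Table 3. All of this is conditional: if heart rate is unrelated to PHQ-9 ≥ 10, nothing goes wrong.

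Two stronger readings do not follow. One is that the HRV objective goes unanswered altogether; the step still answers whether HRV and heart rate together carry information. The other is that heart rate belongs in every model. The primary RI/PI plus baPWV model is unaffected, and nothing here shows a fault in the vascular tiers.

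**What to change.** For the HRV step only, prespecify a second comparison with resting heart rate on both sides:

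- Section 3.5.4: Model B + heart rate against Model C + heart rate;
- Table 3A: Model 2 + heart rate against Model 3 + heart rate;
- Table 3B: the same for its Models B and C.

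Report the AUC change and the SDNN and RMSSD estimates with and without heart rate. State in advance that HRV will be said to add information beyond clinical variables only if the contribution persists with heart rate included. Leave Model A, Model 1 and the primary model as they are.

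The cost is wording and a few table rows, plus one more parameter in these secondary models. The data are already to be collected, the enrolment target does not change, and with no participants enrolled at submission the change is still prespecified. The downside is that heart rate is partly autonomic, so the HRV gain may look smaller after adjustment. Showing both versions covers that.

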### Sample size and effect size estimation

3.6

The primary outcome is concurrent depressive symptom burden defined as PHQ-9 ≥ 10. The primary exposures of interest are dorsalis pedis artery Doppler indices, including resistive index and pulsatility index, together with arterial stiffness measures such as brachial–ankle pulse wave velocity.

Previous studies in populations with functional dyspepsia or chronic gastritis have reported a prevalence of PHQ-9 ≥ 10 in approximately 20%–30%. Although specific data in CAG are limited, we conservatively assume a similar prevalence, and the expected prevalence of moderate-to-severe depressive symptoms in our study sample is estimated at 25%.

To ensure model stability in multivariable logistic regression, we adopt the empirical rule of at least 10 events per variable (EPV ≥ 10). This sample size also permits estimating the prevalence of PHQ-9 ≥ 10 with acceptable precision (95% CI) in clinic-based CAG populations. Given that we plan to include approximately 10–12 covariates (including key vascular exposures and confounders), a minimum of 100–120 events (i.e., participants with PHQ-9 ≥ 10) is required. Assuming a 25% event rate, this translates to a total sample size of approximately 400–480 participants. Accounting for potential 10% missing data or incomplete assessments (e.g., partial vascular/HRV measurements), the target enrollment is set at 450–520 participants. Missingness will be summarized by variable and mechanism will be explored. Multiple imputation by chained equations (MICE) is used for covariates (and exposures if missingness is non-negligible), with the outcome included in the imputation model. Primary analyses report MI estimates; complete-case analyses are presented as sensitivity analyses.

If the observed prevalence of PHQ-9 ≥ 10 is substantially lower than anticipated and the number of events is insufficient for the prespecified multivariable model, we will reduce model complexity by prioritizing predefined core predictors and, if necessary, use penalized regression approaches to improve model stability.

### Missing data handling and internal validation

3.7

Missingness is summarized by variable. The primary outcome is not imputed; however, the outcome is included as a predictor in the imputation models for covariates/exposures. Multiple imputation by chained equations (MICE) is used for covariates (and for exposures if missingness is non-negligible and plausibly missing at random), with the outcome included in the imputation model. Primary analyses report pooled estimates from imputed datasets, while complete-case analyses are presented as sensitivity analyses.

If missingness is high, we may simplify the model or transparently report limitations.

To assess model robustness and avoid overfitting in multimodal classification models for identifying PHQ-9 ≥ 10 at baseline, internal validation is performed using bootstrapping (e.g., 500–1,000 resamples) to obtain optimism-corrected performance metrics (AUC, calibration slope/intercept, Brier score). Corrected AUC values and 95% CIs are calculated, and model performance variability across samples is examined. These results help evaluate the generalizability of the model and will be discussed in the final manuscript. Sample size is driven by model stability and planned internal validation. Assuming ∼15%–25% prevalence of PHQ-9 ≥ 10, the expected number of events will support parsimonious models with prespecified key predictors, with shrinkage/internal validation to mitigate overfitting.

### Data management and confidentiality

3.8

All participant data are de-identified and assigned a unique study ID. The key linking personal identifiers to study IDs is stored separately and securely at each local site, accessible only to authorized site investigators. Electronic Data Capture (EDC) systems with password protection and audit trails are used for data entry. Data transmission between centers and the lead center is encrypted. All paper-based records (e.g., informed consent forms) are stored in locked cabinets at participating sites. Data quality checks (e.g., range checks, logic consistency) are performed regularly by the data management team at the lead center.

### Ethics and dissemination

3.9

At the time of submission, ethical approval has been obtained from the Ethics Committee of the China Academy of Chinese Medical Sciences (No. 2025-EC-KY-004) and Hengshui Hospital of Traditional Chinese Medicine (No. 2025-KY-18). Recruitment at any additional participating site will commence only after site-specific ethical approval and local authorization have been completed. The study will be conducted in accordance with the Declaration of Helsinki. All participants must provide written informed consent before enrollment. The results of this study will be disseminated through peer-reviewed publications and conference presentations.

## Planned presentation of results

4

As this is a study protocol, no results are reported. This section briefly outlines the prespecified analytic domains and the general approach to presenting the study findings after study completion.

### Baseline characteristics

4.1

Baseline characteristics of the enrolled CAG cohort will be summarized overall and by PHQ-9 screening status (<10 vs. ≥10). These descriptive data will include demographic characteristics, lifestyle factors, comorbidities, histological and endoscopic severity, and questionnaire-based symptom measures. Baseline comparisons will be presented primarily descriptively, with standardized mean differences used where appropriate to characterize between-group imbalance.

### Descriptive comparison of multimodal measures by PHQ-9 screening status

4.2

Multimodal measures will be described according to PHQ-9 screening status. These measures will include dorsalis pedis ultrasound indices, arterial stiffness and peripheral vascular indices, autonomic parameters, and questionnaire-based symptom measures. The primary descriptive comparison will remain PHQ-9 < 10 versus PHQ-9 ≥ 10. Additional analyses across broader PHQ-9 severity categories may be presented as exploratory analyses when appropriate.

### Prespecified multivariable association analyses

4.3

Prespecified multivariable analyses will examine the associations between vascular and autonomic measures and depressive symptom burden. The primary model will use PHQ-9 ≥ 10 as the binary outcome in logistic regression. Secondary analyses may additionally examine PHQ-9 total score as a continuous outcome. Effect estimates will be reported with corresponding confidence intervals, with interpretation focused on effect size, precision, and consistency rather than on isolated statistical significance.

### Internal evaluation of prespecified models

4.4

Prespecified models incorporating clinical, vascular, and autonomic variables will be internally evaluated for their ability to identify PHQ-9 screening-positive depressive symptom burden. Discrimination and calibration measures may be summarized to describe model behavior within the study sample, with internal validation used to limit overinterpretation. Any threshold-based summaries will be treated as exploratory and will not be interpreted as ready for immediate clinical implementation.

## Discussion

5

### Principal findings and study contributions

5.1

The main contribution of this protocol is to examine whether vascular and autonomic measures may serve as adjunctive markers of depressive symptom burden in a routine gastroenterology setting, particularly among patients who primarily present with somatic complaints. Rather than replacing standard psychological assessment, the study is intended to evaluate whether these physiological measures may provide additional clinically interpretable information within a histologically defined CAG population.

Previous research has consistently demonstrated a stable comorbidity pattern between upper gastrointestinal (GI) disorders—such as gastritis and functional dyspepsia—and psychological symptoms, including depression and anxiety. A network analysis by Tang et al. (21) in patients with chronic gastritis revealed that anxiety and depressive symptoms often cluster as core nodes within symptom networks, closely connected to multiple gastric complaints. Within this broader spectrum of chronic gastritis, CAG represents a precancerous subtype that may exhibit particularly persistent symptoms and psychosomatic burden, which motivates the present CAG-focused protocol. This supports the view that the “gastric–emotion” relationship is not merely incidental, but instead represents a structured psychosomatic coupling. Furthermore, large-scale Mendelian randomization studies have provided bidirectional causal evidence between depression and various GI diseases, lending genetic-epidemiological support to the concept of a two-way “emotion–gut” interaction (22, 23).

Building upon this foundation, the core hypothesis of our study is that hemodynamic characteristics of the dorsalis pedis artery and systemic arterial stiffness parameters are independently associated with depressive symptom burden in patients with CAG, a precancerous subtype of chronic gastritis, within a broader exploratory multimodal framework involving gastrointestinal, vascular, autonomic, and symptom-related measures. Recent research on vascular dysfunction has expanded beyond large-vessel stiffness to include microvascular abnormalities. Prior studies have reported associations between macrovascular or microvascular impairment and depressive symptoms in some populations (20, 24, 25), although these findings do not establish the specific mechanistic role of dorsalis pedis hemodynamics in the present study setting.

If observed, such associations would be interpreted as cross-sectional correlates within this multimodal framework rather than as evidence of a specific mechanistic pathway, and could help inform future longitudinal validation.

Separately, studies by Wang et al. (26), Galin et al. (27) have consistently shown that patients with depression exhibit reduced heart rate variability (HRV), with HRV indices inversely correlated with depression severity, indicating a significant role for autonomic imbalance in the pathogenesis of depression (28). Our proposed study will jointly analyze HRV metrics, arterial function, gastritis pathology, and depressive symptoms. If these findings are replicated, and if model performance improves after the addition of vascular and autonomic variables beyond clinical and gastrointestinal measures alone, this would support further evaluation of a multimodal assessment framework in future studies.

It must be emphasized that this is an exploratory observational study. Any findings, if validated, are intended primarily to provide a preliminary multimodal evaluation framework and a basis for hypothesis generation, rather than definitive conclusions about causality.

